## Qualitative interview data collection

Data on mechanisms of impact, context, intervention and trial acceptability will be gathered via semi-structured interview. These data will be supplemented with other data from the trial as outlined within Table 2.

### Sample size

For the qualitative interviews we anticipate sampling:

- ~ *n*=15 People living with MLTCs and frailty
- ~*n*=15 Carers
- ~*n*=15 HCPs (physical activity officers and other link workers or community providers involved in the intervention)

As we are examining variation in data, data saturation is not an appropriate criterion for judging the point at which data collection might cease. Information power will be assessed throughout, and the final sample size determined by its ability to provide rich data which addresses the stated aims^110^.

### Sampling technique

Maximum variation sampling of participants will primarily be guided by:

- Level of frailty for people living with MLTCs and frailty (the latter dichotomised as ≥2 LTCs or ≥3 LTCs, the latter being an indicator of complex multimorbidity)^111^.
- Caring circumstances (e.g., multigenerational households) and relationships (e.g., spouses, adult children) for carers
- Role and level of experience for HCPs

These characteristics will be determined from the demographic questionnaire that participants will be asked to complete following consent^112^. As an initial guide for participant recruitment across the different populations of interest, Table 3 shows the preliminary sampling frame developed, with the quotas of participants required in each category to guide recruitment^113^. For all groups, other important characteristics (e.g. sex, age, ethnicity, level of engagement with the intervention (carers and people with MLTCs) and location (areas of high and low socioeconomic deprivation for HCPs) will be monitored on an ongoing basis as recruitment and analysis progresses^112^.

Table 3 Preliminary sampling frame for the PERSONAL-AGILITY trial.

| **Population** | **Criteria** |  | **Proposed quota within the sample** |
| --- | --- | --- | --- |
| People living with MLTCs and frailty | Frailty status | Very mild/mild (CFS 4-5 or eFI >0.12–0.24) | 5 |
|  |  | Moderate  (CFS 6 or eFI >0.24–0.36) | 5 |
|  |  | Severe  (CFS 7 or eFI >0.36) | 5 |
| Carers | Caring circumstances and relationship | Spouse | 5 |
|  |  | Adult child | 5 |
|  |  | Part of a multi-generational household | 5 |
| Health and care professionals | Role | physical activity officer or associated role | 2-7 |
|  |  | Community provider or associated role | 7-12 |

## Recruitment and consent

### People living with MLTCs and frailty, and carer participants

People living with MLTCs and frailty and carer participants will be identified and recruited as described for the feasibility trial (see section 6.2). As part of the consent process for the feasibility trial participants will be informed that they may be contacted regarding their participation in an interview, but that this is optional, and they may decline to take part in this aspect of the study if they wish. The details of the interviews will be provided to participants in a separate participant information sheet to that used for the main study. People living with MLTCs and frailty and carers will be consented separately for the interviews.

### Health and care professionals

Eligible HCPs physical activity officers and other link workers or community providers involved in the intervention) will be approached by the qualitative research team and invited to take part in a semi-structured interview. Those interested in taking part will be provided with an information sheet. When a potential participant has indicated willingness to be interviewed, the researcher will arrange a convenient time and location to obtain informed consent.

## Consent procedures for the interviews

Consent procedures for the interviews will mirror those for the feasibility trial. Given the low-risk nature of the interviews, a proportionate approach to obtaining informed consent that allows for in person or online/telephone consent (as described in section 6.2) for the trial will be taken. This will allow a wider range of participants to take part and will also ensure that an undue burden is not created.

A PIS relating to the interviews will be provided (via email, post or in-person) to potential participants who have expressed an interest in participating in this part of the study. They will also be provided with the researchers’ contact details and encouraged to contact the researchers to discuss any questions or concerns they may have. The researchers will contact potential participants (via email, telephone, in person, or online via secure software e.g. Zoom or Teams) after at least 24-hours to discuss any questions or concerns they may have, confirm their eligibility, and to seek verbal consent to participate.

For in person interviews consent will be obtained by a trained researcher prior to commencing data collection. The researchers will begin by explaining the purpose of the study and details of what participation is required and then participants will be given the opportunity to ask questions and clarify their understanding before being asked to sign a consent form in the presence of the researchers; the participant will be given a copy of the information sheet and consent form to keep for their records and the researchers will keep a signed consent form.

For telephone or online individual interviews, participants will be talked through the consent form prior to commencing data collection. The researcher will initial the boxes in a bespoke consent form and sign on behalf of the participant. A copy of the completed form will be sent to the participant and the original retained in the trial master file. A separate consent form has been created for this process.

## Qualitative data collection for both people with MLTCs and frailty, and health and care professionals

One-to-one semi-structured interviews will be used to gather qualitative data as they offer an open and flexible method for exploring the participants’ individual experiences in-depth. For people living with MLTCs and frailty and their carers, interviews will explore:

- The acceptability of key trial procedures, outcome measures and exploration of any unintended harms and consequences
- The acceptability of the intervention including, where applicable:
  - exploration of the influence of interaction between participants who took part as a ‘dyad’
  - the inclusion of physical activity officer and engagement with community groups
  - barriers and facilitators to engagement
- potential mechanisms of intervention impact
- how contextual factors influenced intervention impact, including any unintended consequences

 Health and care professional interviews will explore:

- Their perceptions of PERSONAL-AGILITY, including its delivery and the need for any adaptations
- How contextual influences hindered or facilitated implementation

Basic demographic data, including (but not limited to) age, gender, ethnicity, profession and years of experience will be collected for HCPs. For individual participants interviews will occur after the 24-week visit or when participants withdraw from the study, if they remain willing to participate in an interview. Participants will have had sufficient experience of the PERSONAL-AGILITY intervention at this stage. Interviews with people with MLTCs and frailty and carer will be conducted separately to allow free expression of views.

Interviews will occur at three time points within the trial:

- After the first six months of recruitment, to identify initial challenges
- Midway through recruitment
- Within the last six months of the study, to identify any ongoing challenges.

Four different preliminary semi-structured topic guides have been developed reflecting the different groups we wish to include in the interviews: people living with MLTCs and frailty (appendix D), carers (appendix E) and physical activity officers (appendix F) and community providers (appendix G). These topic guides have been developed with the PPIE group and the TSG and guided by the PERSONAL-AGILITY programme theory and Normalisation Process Theory (NPT). Normalisation Process Theory is a middle-range implementation theory that has been used extensively to explore the processes underpinning implementation, embedding and integration of service innovation, and is well suited to multi-level intervention evaluation ^107^, ^106^. The first three interviews will act as pilots (but will be included within the overall analyses) and following these the guide may be adjusted. Guides will also be subject to adjustment as the trial progresses and the intervention is refined.

Interviews will be conducted by a trained researcher at an appointment separate from the other trial assessments. They will be arranged around participants’ personal and work commitments. Where possible, participants will be offered an opportunity to choose where the interview takes place either face-to-face, or remotely via telephone or secure online software. Interviews will be led by trained members of the research team. During the interviews, the researcher will introduce the process, explaining the background, how the interview will proceed, and details of audio-recording and note-taking. Participants will be reassured about the preservation of their anonymity and confidentiality as well as being given the opportunity to ask questions before audio-recording commences.

Interviews are anticipated to last approximately 60-90 minutes, depending on what participants wish to share, and the depth of discussion. Researchers will keep field notes during the interviews and observe non-verbal cues and facial expressions which may prompt further questions or follow-up. At the end of each interview, participants will be given another opportunity to ask questions, or seek clarification and the voluntary nature of their participation will be reiterated. Should any participant request further information or highlight any concerns during the interview then these will be discussed with the PI, for appropriate onward referral as required. All participants will be made fully aware of the contact details for the research team, should they have any concerns following the interview.

## Withdrawal criteria

Participants may withdraw from (a) complying with the allocated study treatment and/or (b) providing data to the study, at any time for any reason without affecting their usual care. Participants may withdraw from the process evaluation but remain within the main trial, should they wish. For participants who enrol as a dyad either individual may continue to be involved in the trial should the other person opt to withdraw.

In addition, the PI may discontinue a participant from the study at any time if considered necessary for any reason including:

- Discovered ineligibility which was overlooked at screening/baseline
- Major protocol deviation
- Significant non-compliance with treatment regimen or study requirements
- Participation in another intervention research study
- An AE which results in inability to continue to comply with study procedures
- Disease progression which results in inability to continue to comply with study procedures
- Prolonged or serious hospital admission (at the discretion of review by a study clinician)
- Development of any of the conditions or circumstances outline in the exclusion criteria

Withdrawals from the trial will be recorded in the CRF, database and medical records. Participants do not have to give a reason for withdrawal, however if they do provide a reason for leaving the study, this will be documented. If the participant is withdrawn due to an AE, the investigator will arrange for safety follow-up visits or telephone calls until the adverse event has resolved or stabilised.

They will be sent a letter thanking them for their participation and informing them that the data collected up to the time point they withdrew will be included in the trial analysis and that they will not be contacted again with regards to this trial, unless they consent to withdraw from active intervention but remain enrolled for subsequent follow-up. They will not be asked to complete any further study measures. A letter will also be sent to their GP to inform them of their withdrawal in the trial. For participants who are not contactable or fail to return questionnaires/accelerometer, the research team will make reasonable efforts to re-contact the participants (e.g., contacting informal carer if involved in the study or GP, reviewing available health care databases) and to determine their health status. Attempts to contact such participants will be documented in the participant’s records.

If a participant is withdrawn from the study due to a loss of capacity to provide informed consent, then all research data that has been collected prior to withdrawal will be retained. The participant will not be contacted again with regards to the trial, and no further follow-up data will be collected.

Each participant will have a copy of the consent form and participant information leaflet placed in their hospital medical records. A standard label will be used on the front of the medical notes to highlight to any reviewer that this individual is taking part in the study. As this is a feasibility study, one of the primary outcomes will be the proportion of, and reasons for withdrawal and therefore we will not be attempting to replace participants that withdraw.

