## Exclusion criteria

For all participants:

- Unable to provide informed consent
- Unable to communicate in English
- Known contraindications to exercise (as defined by the American College of Sports Medicine)^77^ to include:
  - Unstable cardiac disease (Uncontrolled arrhythmias; unstable angina or heart attack within the last 3 months; persistent uncontrolled hypertension (systolic blood pressure >180 mm Hg or diastolic blood pressure >110 mm Hg); stroke or transient ischaemic attack within the last 3 months)
  - Active infection
  - Significant aortic aneurysm (more than 5.5 cm)
  - Any other condition in which the investigator feel exercise may be contraindicated.
- Current participation in competing clinical trial (as determined by study investigator of this trial).
- Significant cognitive impairment (Mini mental state examination score of less than 24)^78^ or unstable psychiatric disorder that limits active participation in the intervention.
- Serious illness or event with life-expectancy <1year, active malignancy (on chemotherapy/radiotherapy) or other significant illness which, in the opinion of a study clinician, precludes involvement.
- Self-reportedly already regularly engaging in at least 150 minutes of moderate-to-vigorous physical activity per week.

People with MLTCs and frailty:

- Not frail as defined by:
  - eFI:0-0.12 or
  - A CFS score of 1-3 (very fit to managing well).

Carers:

- Providing paid/professional care.

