## Reporting procedures for all Adverse Events

AEs that are deemed directly related to study activities which are observed by the investigator or reported by the participant will be recorded in the participant’s medical records and an AE log from the time the participant is randomised. The following information will be recorded: description, date of onset and end date, severity, assessment of relatedness to study, and action taken. Additional follow-up information should be provided as necessary. AEs considered related to the study as judged by a medically qualified investigator or the sponsor will be followed until resolution, or the event is considered stable.  All related AEs that result in a participant’s withdrawal from the study or are present at the end of the study, should be followed up until a satisfactory resolution occurs.

It will be left to the investigator’s clinical judgement whether an AE is of sufficient severity to require the participant’s removal from treatment. A participant may also voluntarily withdraw from treatment due to what he or she perceives as an intolerable AE.  If either of these occurs, the participant must undergo an end of study assessment and be given appropriate care under medical supervision until symptoms cease or the condition becomes stable. The severity of events will be assessed using the following scale: 1 = mild, 2 = moderate, 3 = severe. AE’s will be recorded within the participant’s medical records and an AE log. Any safety concerns that arise because of this, will be reported to the sponsor as soon as possible.

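### Section 7.8 lets the investigator end study follow-up, not only the intervention, for non-compliance or for meeting an exclusion criterion, so investigator decisions can lower retention and selectively remove week 12 and 24 outcomes

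*Protocol*

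**What the plan says.** Protocol section 7.8 (Withdrawal criteria) opens by distinguishing withdrawal from the allocated treatment from withdrawal from giving data. It then adds a separate power: "the PI may discontinue a participant from the study at any time if considered necessary for any reason including". Among the listed grounds are a major protocol deviation, "Significant non-compliance with treatment regimen or study requirements" and "Development of any of the conditions or circumstances outline in the exclusion criteria".

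Section 5.2 (Exclusion criteria) lists, for people with long-term conditions and carers alike, "Self-reportedly already regularly engaging in at least 150 minutes of moderate-to-vigorous physical activity per week". Section 7.8 exempts none of the exclusion criteria.

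On what follows withdrawal, section 7.8 says data collected so far stay in the analysis and the person is not contacted again, "unless they consent to withdraw from active intervention but remain enrolled for subsequent follow-up". It continues: "They will not be asked to complete any further study measures". Withdrawals because of an adverse event get safety follow-up.

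Three other parts of the protocol bear on this:

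- **Outcomes.** Retention and outcome completion are primary outcomes (section 2.3.1) and progression criteria (section 9.4, Table 5). Section 7.8 itself treats the proportion of withdrawals and their reasons as a primary outcome and rules out replacement. Section 9.5 rules out imputation.
- **Adverse events.** Section 8.2 covers removal from treatment, or voluntary withdrawal from it, because of an adverse event: "If either of these occurs, the participant must undergo an end of study assessment".
- **Incomplete assessments.** Section 16 keeps in the study people who cannot or will not complete secondary assessments, provided they can supply feasibility data.

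**The concern.** A feasibility trial that measures retention needs the count to reflect what participants do. Under section 7.8 part of it can reflect what the PI decides. Someone who adheres poorly but would attend week 24 can be turned into a loss, although poor adherence is one of the things the trial wants to observe and explain.

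The exclusion-criteria ground adds a second problem. Some exclusion criteria describe deterioration or safety. The activity criterion describes the success of an intervention meant to raise activity. As worded, a participant who becomes active enough falls within a ground for discontinuation. If that happens, the week 24 outcome is missing because of its likely value, and section 9.5 does not fill the gap.

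The regimen half of the non-compliance ground falls mainly on the intervention arm, because usual care has no trial regimen to breach. Any selective loss from that half is therefore uneven between arms. At stake are the retention colour in Table 5 and the descriptive 12- and 24-week summaries used to choose a primary outcome for the definitive trial.

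**Working it through.** The protocol gives no precision or power calculation for retention and no expected removal rate, so there is no stated figure to reproduce. The inputs from the protocol are n=50 people with long-term conditions and frailty (section 9.1), 2:1 allocation (section 6.6, about 33 and 17) and green at 70% or more retained at 24 weeks (Table 5). Section 9.3 analyses carers separately, so 50 is the base. Removal numbers and underlying retention below are assumptions. Discontinued participants are taken to count as not retained.

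**Step 1: cost per removal.** 1/50 = 2.0 points overall. Within arms, 1/33 = 3.0 points (intervention) and 1/17 = 5.9 points (usual care).

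**Step 2: removals needed to leave green.** Green needs 0.70 × 50 = 35 retained.

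| Retained without PI removals | PI removals | Retained with them | Colour |
|---|---|---|---|
| 37/50 = 74% | 2 | 35/50 = 70% | green |
| 37/50 = 74% | 3 | 34/50 = 68% | amber |
| 40/50 = 80% | 5 | 35/50 = 70% | green |
| 40/50 = 80% | 6 | 34/50 = 68% | amber |

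**Step 3: chance of a green result.** Let r be underlying retention and q the share of otherwise retained participants whom the PI removes. Then P(green) = P(X ≥ 35), with X binomial(50, r(1 − q)).

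| r | q = 0 | q = 10% | q = 20% |
|---|---|---|---|
| 75% | 0.84 | 0.42 | 0.10 |
| 80% | 0.97 | 0.69 | 0.23 |
| 85% | 0.998 | 0.89 | 0.45 |

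The q = 0 column is also the result if follow-up continues after discontinuation and everyone invited attends.

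**Step 4: loss of outcomes.** Suppose 28 of 33 intervention participants average 80 minutes of activity per week and 5 average 170. The mean is (28 × 80 + 5 × 170)/33 = 3090/33 = 93.6 minutes. If the five are discontinued before week 24 and not measured, the mean of those left is 80.0. These values are invented to show the direction of the shift.

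**Step 5: the passages side by side.**

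- Section 7.8 makes non-compliance with study requirements a possible ground for leaving. Section 16 keeps in people who do not complete secondary assessments. The boundary between the two is not drawn.
- Section 7.8 asks withdrawn participants for no further measures. Section 8.2 requires an end of study assessment after removal from treatment for an adverse event, and the schedule in section 6.1 shows no such visit. Whether removal from treatment also means leaving the study is not stated.

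**The case against.** The strongest reply is that the power is discretionary, tied to what the PI considers necessary, and may rarely be used. The activity criterion speaks of people already active, which describes entry. Section 7.8 already separates stopping treatment from stopping data. Withdrawals and any reasons given are recorded, so PI-led ones can be identified. Section 9.4 says a missed criterion does not by itself end the programme, and section 9.5 plans descriptive summaries without p values. With 37/50 retained, the exact 95% interval is about 60% to 85%, wider than the shift from three removals.

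Much of this stands as a limit on size. It does not remove the problem. The ground that covers developing any exclusion circumstance carries the activity criterion into follow-up. The stay-enrolled route is not expressly linked to PI-led discontinuation. A recorded reason does not recover a missing week 24 measurement. Sampling error is random, whereas removals push retention one way.

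Four stronger readings are tempting, and the documents do not support them:

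- **Engagement is inflated because poor engagers drop out of the average.** Section 7.8 keeps data up to withdrawal in the analysis, and nothing excludes these people from the engagement summary. An upward shift, or a second Table 5 colour changing, cannot be inferred.
- **The distortion sits in one arm.** Non-compliance also covers study requirements, which apply to both arms, as do the other grounds.
- **People who cease to be frail will be removed.** A Clinical Frailty Scale score of 1–3 is on the exclusion list, but the scale is not scheduled at weeks 12 or 24, so no planned assessment would detect it.
- **Section 8.2 says the opposite of section 7.8.** It concerns removal from treatment, while section 7.8 concerns leaving the study. This is an inconsistency to reconcile.

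**Conclusion.** The concern holds as a defect in how section 7.8 treats follow-up after PI-led discontinuation. As written, the PI may end a participant's follow-up for non-compliance, for a major deviation or for meeting any exclusion criterion, including the activity level the intervention aims at. This can only lower retention. The cost is 2 points per removal at n=50, and three removals are enough to take 37/50 from green to amber. With 80% underlying retention, removing 10% of those otherwise retained cuts the chance of green from 0.97 to 0.69. It can also remove week 12 and 24 outcomes selectively, with no imputation.

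The size is uncertain, because the protocol gives no expected removal rate and every removal number here is assumed. The conclusion also assumes that discontinued participants count as not retained and that the stay-enrolled route is not applied to them. If it were applied routinely, most of the problem would disappear, so making it the default is the remedy.

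**What to change.** Leave decisions on stopping the intervention with the clinical team, as now, and change what follows them:

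1. State in section 7.8 that anyone whose intervention is stopped, by their own choice or by the PI, is by default invited to the week 12 and 24 assessments they can safely do, unless they withdraw consent to follow-up or lose capacity.
2. State that all randomised participants stay in the denominators for retention and outcome completion.
3. Report PI-led and participant-led withdrawals separately, with reasons, by arm.
4. Reconcile the blanket exclusion-criteria ground with the intervention's intended effects, in particular the activity criterion. The safety-related grounds need not be struck out.
5. Reconcile section 7.8 with section 8.2 on the end of study assessment after an adverse event, and with section 16 on people who do not complete secondary assessments.

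The cost is a wording amendment and a few extra follow-up visits. It needs to be in place before participants are discontinued, because missed assessments cannot be recovered later.
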